## Abstract

**Background:**

Reablement is a time-limited intervention that aims to support people to regain independence and enable them to resume their daily activities after they return home from an in-patient care setting, or to maintain independence to enable them to remain at home. There is some evidence that reablement can enhance independence and has the potential to contain costs. However, reablement services are funded and provided in different ways and by different organisations, and there is limited research evidence about the effectiveness of different reablement service models. This study will evaluate the effectiveness and cost-effectiveness of different reablement service models and service users’ and carers’ experiences of reablement in England, UK.

**Methods/Design:**

The study will use a quasi-experimental mixed methods design that comprises three work packages (WP) extending over a period of 34 months. WP1 will conduct cluster analysis on survey data to develop a typology of current models of reablement services in order to describe the current reablement service landscape. WP2 will comprise a quantitative outcomes evaluation of the effectiveness of the different service models; a process evaluation and an economic evaluation. WP2 will be set within generic reablement services, where providers are using the most commonly employed generic reablement service types identified in WP1; the primary outcome measure is health-related quality of life measured by the EQ-5D-5L. WP3 will provide evidence about specialist reablement services and how specialist approaches and practices are organised and delivered.

**Discussion:**

Managing demands on care services is, and will remain, a crucial factor for the UK National Health Service as the number of people with long-term conditions rise. There has been, and will continue to be, significant investment in reablement services. The proposed study will address several key areas where there is limited evidence regarding the organisation and delivery of reablement services in England, UK. Specifically, it will provide new evidence on different models of reablement services that will be of direct benefit to health and social care managers, commissioners and their partner organisations.

**Electronic supplementary material:**

The online version of this article (doi:10.1186/s12913-016-1600-6) contains supplementary material, which is available to authorized users.

## Background

A rapidly ageing population and advances in technology have led to a dramatic rise in the number of people living longer with long-term conditions that affect their ability to live independently [1, 2]. This has resulted in a significant rise in hospital admissions and increasing pressure on social care services including intermediate care and community services [3]. Improvements in care in some childhood conditions have led to increasing numbers of young people with complex needs surviving into adulthood [4]. Attempts to bring about a real shift to community-based care and avoid unnecessary/lengthy hospital admissions or ‘unnecessary dependency’ on social care services have long dominated health and social care policies and strategies in the UK and other countries [5–7].

Reablement is a relatively new approach that aims to support people to regain or maintain independence in their daily lives [8]. The reason for referring an individual to a reablement service can be conceived as falling into one of two broad categories: to support an individual to return home from hospital or other in-patient care setting following an acute episode; or to support an individual to remain at home, with minimum demands on home-care/community services, where there is evidence of declining independence or ability to cope with everyday living [9]. Reablement is a time-limited intervention to help enable people to resume the everyday activities which make up their daily lives for example, cleaning the house, shopping or bathing and dressing themselves independently rather than having someone (such as an informal or formal carer) do things ‘to’ them or ‘for’ them [8, 9].

The key characteristics that have been identified [10], which distinguish reablement from other health and social care services are, the time-limited nature of the service, that it contains a restorative/self-care element and that it aims to achieve some (or all) of the following five service objectives: acute admission avoidance at the point of clinical need for acute care; early supported discharge after acute admission; longer-term avoidance of unplanned hospital admission; reduction in the use of home care services; avoidance of admission to long-term care.

The UK government has invested substantially in reablement services as there is some evidence that they can enhance independence and have the potential to contain costs [11]. This was signalled by £70 million extra funding made available to the UK National Health Service (NHS) in 2010 to support hospital discharge [12], followed by £300 million/year over 2012–15 for ‘reablement spending’ [13]. More recently, the UK government announced an investment of £91.6 billion in local NHS services in 2012/3, including £150 million for reablement [14]. The promotion of reablement services within the Care and Support 2012 White Paper has also firmly established it as a priority for local authorities [15].

While existing research suggests that reablement can lead to improvements in health-related quality of life, social care outcomes and physical functioning and remove or decrease the need for commissioned health and home care services [11, 16], the evidence base around reablement services remains limited and significant questions remain. The rapid development of reablement services in England (UK) has created variation in the service landscape. Differences in how services are funded and delivered by different organisations and their effectiveness on service user outcomes cannot be addressed by the existing body of research in this area [11]. Reablement is reported to work differently for different people, being less effective for those with chronic/complex health problems compared to people recovering from acute illnesses or falls [17]. Considerable variation is also reported in local arrangements for self-care services for long-term conditions [18]. Indeed, for some groups (e.g. young adults with life-limiting conditions and adults with dementia), the evidence base is virtually non-existent. Evidence suggests that the number and proportion of people with specialist needs is growing fast. For example, the number of people living with dementia in the UK is expected to double in the next 30 years while the overall costs of dementia in the UK are estimated to triple from £17 billion per year to over £50 billion [19]. The rapid rise in the number and proportion of people with specialist needs suggests that responding to such needs will become an ever-growing pressure on health and social care services. It is, therefore, important that both those populations that access ‘generic’ reablement services as well as those with specialist needs are represented in this research.

This study will evaluate: whether the type of service model affects services users’ outcomes; what other factors, such as age and other medical conditions, affect the effectiveness and cost-effectiveness of different reablement service models; and service users’ and carers’ experiences of reablement.

## Methods/Design

The primary aim of this study is to evaluate different models of reablement services, which will generate evidence to support commissioners and practitioners as they make decisions about the organisation, delivery and development of reablement services. The study comprises three work packages using different methods and data collection strategies extending over a period of 34 months. These are:Work package 1 (WP1): Mapping reablement services.Work package 2 (WP2): Evaluation of generic reablement service models.Work package 3 (WP3): Description of specialist reablement services/practice approaches.

To avoid confusion between the use of the term ‘model’ to describe service configuration (i.e. service model) and statistical techniques (i.e. modelling), the term ‘service type’ has been used instead of ‘service model’ throughout the methods section.

### Work package 1 (WP1): mapping reablement services

Work package 1 (WP1) will generate ‘stand-alone’ evidence on reablement services in England and develop a typology of current types of reablement services. The typology will be used to identify four service types for evaluation. It will also be used to fine-tune the design and sampling of WP2 and WP3. It will employ survey methodology comprising a three-stage process: a) identification of reablement services; b) identification of key informants in each reablement service; and c) data collection from key informants of reablement services.

### Methods – WP1

Identification of reablement servicesThe first stage of WP1 will involve an initial screening exercise to identify the person most closely involved with commissioning intermediate care/reablement services in every Clinical Commissioning Group (CCG) (*n =* 221) or Local Authority (LA) with responsibility for adult social services (*n =* 154) in England. Some of these key informants may commission joint services, others may have more than one service, and a few may have none, so the total number of *services* surveyed is expected to be approximately 375. The people identified as the key informant in each service will be contacted by telephone and asked about services that they commission that serve any, some or all of the five objectives of intermediate care/reablement [10].Identification of key informants in each reablement serviceIndividuals identified as the key informant most closely involved with commissioning intermediate care/reablement services in every CCG or LA with responsibility for adult social services that serve any, some or all of the five objectives of intermediate care/reablement [10] will be asked to provide contact details for the managers of these services. Managers of the service will be contacted by telephone to: confirm the objectives of their service; that they operate in a time-limited form; and include some element of restorative input. This will establish whether the manager identified by the commissioner is the person best placed to answer detailed questions about the service delivery and organisational characteristics of the service.Data collection from key informants of reablement servicesA structured questionnaire will be administered using electronic survey software to each of the identified key informants of each reablement service. It will cover a range of service delivery and organisational characteristics that research with service managers, practitioners and users suggests are important in influencing outcomes in these types of services [11, 20, 21]]. Where there are cases of non-response or where answers are unclear or ambiguous, respondents will be followed-up via telephone contact.

#### Analysis

Survey data will be analysed descriptively as a first stage, to give a simple national picture of current reablement provision. Cluster analysis [22] will be used to develop a typology of reablement services using data on the characteristics of the services. The service delivery and organisational variables collected from the survey will form the basis for analysis. Cluster analysis is a useful way of developing a tight typology of services in order to assist analysis of differences and similarities between services, while at the same time preserving the underlying features of individual services. The typology of services will be tested using bivariate analysis to ensure that it does differentiate between different types of reablement service types. A second cluster analysis will also be undertaken using the survey data on case mix, size and eligibility, to categorise the different service user groups served by reablement services. The results of the cluster analysis will stand in their own right as a typology of reablement services but will also inform sampling of services for the next stage of the research, when the study will focus on the differential impact of specific service types.

WP1 has been completed and four generic reablement service types have been identified for evaluation in Work package 2. The findings from WP1 will be reported elsewhere.

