### Methods – WP2a

#### Setting

WP2a will evaluate four types of reablement services identified in WP1 above. WP2a will be set within generic reablement services, where providers are using the most commonly employed generic reablement service types across England (UK) as identified in WP1. This should ensure a meaningful and applicable evaluation with findings transferable to other settings.

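### The only stated check on the typology, bivariate testing, would usually be passed even if no distinct service types existed, so a pass does not validate the four compared groups

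*Protocol article*

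**What the plan says.** All passages are in the protocol article.

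- **How the types are formed** (WP1, Analysis): "Cluster analysis [22] will be used to develop a typology of reablement services using data on the characteristics of the services". On the inputs: "The service delivery and organisational variables collected from the survey will form the basis for analysis".
- **How they are checked** (same section): "The typology of services will be tested using bivariate analysis to ensure that it does differentiate between different types of reablement service types". The section does not list the variables tested and describes no other check.
- **Other survey items** (same section): "A second cluster analysis will also be undertaken using the survey data on case mix, size and eligibility". These items serve to classify user groups. They are not named as a check on the first clustering.
- **Survey size** (Methods – WP1): the number of services "surveyed is expected to be approximately 375".
- **How the types are used** (WP1 introduction): "The typology will be used to identify four service types for evaluation". Under Setting: "WP2a will evaluate four types of reablement services identified in WP1 above". The economic evaluation (WP2c) compares the same four types for value for money.
- **Status** (WP1, Analysis): "WP1 has been completed and four generic reablement service types have been identified for evaluation in Work package 2". Detailed findings are to appear in a separate report.

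**The concern.** Cluster analysis divides services so that they differ on the variables fed to it. Testing those variables across the resulting groups uses the same data twice, and the nominal error rate no longer applies. Clear differences then appear even when one homogeneous population has been cut into arbitrary pieces. The article gives this step the job of making sure that the typology separates services, and the step cannot do that job.

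The typology is the exposure in WP2a and WP2c. If its boundaries are arbitrary or unstable, a commissioner cannot tell which type a given service belongs to. A null result in WP2a then could not be read as showing that type makes no difference, and a positive result could not safely be carried over to other services with the same label.

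**Working it through.** The article gives no figure for the check, so there is none to reproduce. The question is how often the check is passed when there are no types.

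**Inputs from the article.** 221 Clinical Commissioning Groups + 154 Local Authorities = 375, the expected number of services. Four types are evaluated.

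**Assumptions.** The article gives no algorithm, number of items, response rate or significance level for this step. I took four clusters, 8 to 20 clustering items, 100 to 375 services and a 0.05 level (the article states 0.05 only for the WP2a sample size).

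**Method.** Generate one homogeneous population with no types. Cut it into four clusters. Test each variable across the clusters by one-way ANOVA (continuous items) or chi-square (binary items). Record the share with p < 0.05, both for the clustering variables and for other items in the same survey. If the tests kept their level, the share would be 5%.

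**Result 1: k-means, independent normal items, 200 replicates.**

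| Services | Clustering items | Clustering variables with p < 0.05 |
|---|---|---|
| 375 | 8 | 98.3% |
| 375 | 15 | 94.9% |
| 150 | 8 | 94.1% |
| 150 | 15 | 84.8% |

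On variables unrelated to the clustering items the share was 4.4% to 5.6%.

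**Result 2: k-means and Ward, continuous and binary items, 10 or 20 clustering items, 100 replicates per setting.** Ranges run over these choices.

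| Item correlation | Services | Clustering variables | Other survey items |
|---|---|---|---|
| 0 | 375 | 77.5–98.6% | 3.6–6.0% |
| 0 | 200 | 79.8–95.1% | 3.2–6.2% |
| 0 | 100 | 68.8–90.3% | 3.2–7.0% |
| 0.2 | 375 | 99.9–100% | 94.2–100% |
| 0.2 | 200 | 98.2–100% | 68.8–100% |
| 0.2 | 100 | 90.0–99.2% | 41.4–90.4% |

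A correlation of 0.2 here means that all items share one continuum, still without types. Items describing the same service can plausibly be related to that degree, but the article gives no figure.

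**Result 3: does a stability check behave differently?** I re-clustered bootstrap samples from populations with no types (four clusters; 375 or 150 services; item correlation 0 or 0.2) and compared the assignments by the adjusted Rand index, where 1 is perfect agreement and 0 is chance. The index was 0.14 to 0.44. In the same settings the bivariate tests on clustering variables were positive for about 85% to 100% of variables, and on other items correlated 0.2 for 93% to 100%. The stability check gave a warning where the bivariate check did not.

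**Sites per type.** Under Sample size, the article plans about 200 people per type (800 in total) and takes an average cluster size of 200. Its design effect confirms the size used: 1 + (200 − 1) × 0.007 = 2.393. If a cluster is a site, 800 / 200 = 4 clusters, or about one per type. The number of sites is not fixed in the article, so this is an inference.

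**The case against.** - **The tested variables are not stated.** True. A reader might infer that the tests certainly use the clustering variables and are therefore circular. The text does not settle this: the survey also held case mix, size and eligibility items. The concern survives because modestly correlated survey items are also mostly positive without types. If the tested items were unrelated to the clustering items, the tests would keep their 5% level.
- **The check can fail.** A reader might conclude that it cannot. The simulations do not support that: in some settings about 30% of clustering variables did not differ. The right statement is that it almost always passes.
- **The step is descriptive.** Bivariate profiles do show which characteristics separate the groups, and that use is sound. But the article says that the step tests the typology, which is more than description.
- **The simulation is not the trial's method.** The algorithm and item types are assumed, and 375 is an expected count, not a count of responders. Four may also be a selection from a larger typology, since Setting speaks of the types in commonest use. The result held across two algorithms, two item types and smaller samples.
- **WP1 is complete and reported elsewhere.** Other checks may have been made. This article states only this one.
- **Harm to WP2a is not shown.** This stands. The simulations do not show that the trial's types are unreal, that services are misclassified or that effects are diluted, and the comparison of the sampled services is not itself biased.
- **Other parts of the study help.** Survey items were chosen because earlier research linked them to outcomes, and WP2b adds interviews on service structure. These support relevance but do not test whether the grouping is stable.

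**Conclusion.** The point holds in this form: the article's only stated check on the typology does not show that the types are real or stable. With no types present, about 85% to 100% of clustering variables test positive (four clusters, 150 to 375 services, assumed k-means and normal items). The range widens to about 69% to 100% across the other algorithms, item types and sample sizes tried. Other survey items correlated 0.2 are positive 94% to 100% of the time at 375 services and 41% to 100% at 100 to 200.

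It would go too far to infer that the four types do not exist or that the WP2a outcome comparison is invalid. What is weakened is the meaning of the type labels, and with it the step from the sampled services to types in general. The point merits a change because the typology defines the groups in both WP2a and WP2c and the remedy is available from data in hand.

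**What to change.** 1. Keep the bivariate results only as a description of the clusters, name the variables tested, and do not present the p-values as validation.
2. As the validation, re-cluster bootstrap or split-half samples of the existing WP1 survey data. Report the adjusted Rand index and how often each WP2 site keeps its assigned type.
3. If agreement is low, state the WP2a and WP2c results as comparisons of the sampled services, and do not read a null result as evidence that type does not matter.

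Two tempting alternatives should not be relied on. Tests on survey items held out of the clustering are not enough alone, because correlated items pass without types. WP2a analyses that drop unstable sites, or replace type by several service characteristics, should be run only if there are enough sites per type. With about one site per type, dropping one would remove a whole group, and four sites could not support several service-level variables.

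The cost is a small re-analysis with no new data, and possibly more cautious wording of the conclusions.

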### Work package 2 (WP2): evaluation of generic reablement services

Work package 2 (WP2) comprises three elements: an outcomes evaluation (WP2a); a process evaluation (WP2b); and an economic evaluation (WP2c).

### Outcomes evaluation (WP2a)

WP2a outcomes evaluation is a quantitative evaluation of the effectiveness of the different service types, which will examine short and longer-term service-level and individual-level outcomes, and compare outcomes between service types. Quantitative patient-reported and practitioner-reported measures will be used to understand the effects of reablement and the impact of service and user characteristics and other factors on effectiveness.

### Methods – WP2a

#### Setting

WP2a will evaluate four types of reablement services identified in WP1 above. WP2a will be set within generic reablement services, where providers are using the most commonly employed generic reablement service types across England (UK) as identified in WP1. This should ensure a meaningful and applicable evaluation with findings transferable to other settings.

#### Participants – inclusion/exclusion criteria

People referred to reablement services aged 18 and over (no upper age limit is imposed) are eligible to take part in the study if they have been offered and accepted a programme of reablement, and are able to give written informed consent. There are no study exclusion criteria other than lack of capacity to give informed consent [23].

#### Data collection

Service users recruited to the project will be the main source of data collection. Individual participant outcomes will be measured at three time points: within the first week of receiving the reablement service (T_0_); within a week of discharge from the reablement service (T_1_); and 6 months post-discharge (T_2_ = T_1_ + 6 months).

In addition, practitioners conducting reablement service assessments and reablement practitioners will be asked to collect background data on health, functioning and living situation. For each research participant, the reablement practitioner conducting the reablement service assessment (T_0_) will complete a study entry form and information about functional status, which includes questions on: health status; impairments (e.g. memory/confusion; cognitive impairment); living situation (e.g. living alone versus with partner/other family) and informal carer involvement. Services will also be asked to provide the study with routinely collected service delivery/audit data.

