#### Service level outcomes

The reason for referring an individual to a reablement service can be conceived as falling into one of two broad categories: to support an individual to return home (RH) from hospital or residential care setting following an acute episode or to support an individual to remain at home (RAH). Service level outcomes will include the proportion of RH users readmitted to hospital within six months of discharge from the reablement service; the proportion of RAH service users placed in residential care within six months of discharge from the reablement service; and the proportion of RAH service users with reduced use of ‘home care’ type services at six months after discharge from the reablement service.

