#### Outcomes

The cost-effectiveness analysis will consider health outcomes expressed in quality-adjusted life years (QALYs) using EQ-5D-5L collected during WP2a. The cost-consequence analysis will consider QALYs and social care-related quality of life, using the ASCOT SCT-4 collected during WP2a. Both EQ-5D-5L and ASCOT SCT-4 will be valued using the UK population tariffs [37, 38].

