#### Resource use and costs

Resource use will be collected directly from study participants using a bespoke questionnaire, the Service and Care Pathway Questionnaire (SCPQ), collected at T_0_, T_1_ and T_2_. The SCPQ will collect data on the use of health, social care and voluntary services, both publicly funded and privately paid, and informal care. The SCPQ will be piloted with a sample of service users and amended as required prior to the commencement of data collection. Study participants will be asked for their use of hospital services over the previous 6 months. The recall period for other services will be subject to the results of the pilot.

Resource use will be valued with national costs whenever possible. For the services where national costs are not available, the process evaluation in WP2b will obtain the relevant local costs. The cost-effectiveness analysis will include the costs from the perspective of the UK NHS and publicly funded social care. The cost-consequence analysis will include costs falling on all sectors, namely UK NHS, publicly funded social care, voluntary services, private costs and informal care.

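### The readmission and residential-placement outcomes start at discharge from reablement, so events during the service are left out and service types can look different at equal risk

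*Protocol article*

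**What the plan says.** Under Methods – WP2a, Data collection, the baseline measurement is tied to the start of the service: "within the first week of receiving the reablement service (T_0". The later two are tied to its end: "within a week of discharge from the reablement service (T_1_); and 6 months post-discharge (T_2_ = T_1_ + 6 months".

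The section on service level outcomes uses the same end-of-service clock. For people returning home (RH) the outcome is "the proportion of RH users readmitted to hospital within six months of discharge from the reablement service". For people supported to remain at home (RAH) it is "the proportion of RAH service users placed in residential care within six months of discharge from the reablement service". A third outcome, reduced home care, is assessed at six months after discharge.

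The economic evaluation uses "the Service and Care Pathway Questionnaire (SCPQ), collected at T_0_, T_1_ and T_2". On hospital use it adds: "Study participants will be asked for their use of hospital services over the previous 6 months". The recall period for other services is left to a pilot. QALYs are to come from the EQ-5D-5L collected in WP2a; the article states no time window for them.

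**The concern.** Discharge from reablement is not a baseline event. It follows exposure to the service under evaluation, and its timing may reflect how that service operates. A window that opens there has two consequences.

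- **Omission.** An RH user readmitted in the second week of reablement, or an RAH user placed in residential care before discharge, is not an event under the definitions given. Yet the Background lists avoiding hospital admission and long-term care among the objectives of reablement.
- **Unequal windows.** If one type keeps users longer, its six-month window opens later in their recovery. Where risk falls over time, the longer service is scored on a lower-risk stretch. Where in-service event rates differ, that difference does not show at all.

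These proportions are compared between types, and the study's stated purpose is to inform commissioners' choices. A gap produced by where the clock starts could be read as a difference in effectiveness.

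**Working it through.** The plan has no figure of its own to reproduce here. It gives no service lengths, event risks or utilities, so every number below is an illustration on stated assumptions. The sample size is not affected.

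**1. What each window covers.** Let L be the length of reablement.

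- Service-level readmission and placement: from L to L + 6 months after service start. The interval from 0 to L is excluded.
- T0 to T2: about L + 6 months, allowing for the one-week tolerances at T0 and T1.
- Hospital use in the questionnaire: the six months before T1 and the six months before T2. Together these cover the whole of T0 to T2 if L is no more than about six months.

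**2. Same risk, different length.** Assume the same readmission hazard in two types: 0.03 a week for the first 6 weeks from start, then 0.01 a week. One service lasts 2 weeks, the other 6. Six months is taken as 26 weeks. Risk = 1 − exp(−cumulative hazard).

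- After discharge, 2-week service: 4 × 0.03 + 22 × 0.01 = 0.34; 1 − exp(−0.34) = 28.8%.
- After discharge, 6-week service: 26 × 0.01 = 0.26; 1 − exp(−0.26) = 22.9%.
- During the service, outside the outcome: 1 − exp(−2 × 0.03) = 5.8% and 1 − exp(−6 × 0.03) = 16.5%.
- From start, either type: 6 × 0.03 + 20 × 0.01 = 0.38; 1 − exp(−0.38) = 31.6% at 26 weeks.

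The post-discharge measure shows a gap of 28.8 − 22.9 = 5.9 percentage points in favour of the longer service, where no difference in risk exists.

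**3. Constant hazard.** Assume instead a constant hazard h = −ln(1 − r)/26.09 a week, with six-month risk r between 20% and 40%. The share readmitted during the service is 1 − exp(−hL):

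- L = 2 weeks: 1.7% to 3.8%
- L = 6 weeks: 5.0% to 11.1%
- L = 12 weeks: 9.8% to 20.9%

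Here the post-discharge risk equals r whatever the length. Length alone therefore distorts the comparison only if risk changes over time. The omission of in-service events remains in either case.

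**4. QALYs, only if raw T0–T2 totals were compared.** A 4-week difference in L adds (4/52) × 0.4 = 0.031 to (4/52) × 0.6 = 0.046 QALY at assumed utilities of 0.4 to 0.6, with identical health.

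**The case against.** Several points on the other side are sound.

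- **The data are not lost.** A reader might infer that all follow-up runs from discharge and that in-service readmissions are never seen. The article does not support this. T0 is tied to service start, the T1 questionnaire asks about six months of hospital use, and services are asked for routine delivery and audit data. In-service admissions are collected as resource use; they are missing only from the service-level outcome.
- **No difference in length is stated.** Services are described as time-limited and the types were built from delivery and organisational variables, but no durations are given and nothing says that the type fixes the discharge date. If lengths and in-service event rates are similar, the distortion is small.
- **The QALY horizon is unstated, not wrong.** The article says only "health outcomes expressed in quality-adjusted life years (QALYs) using EQ-5D-5L collected during WP2a", and a decision model is to extend the comparison over the longer term. A common horizon may stand in the full plan, as may the coding of time in the multilevel model. Their absence from an article is no fault.
- **Status after the service is a fair question.** EQ-5D-5L six months after a time-limited service has ended is a legitimate measurement, as is home-care use at that point.

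What these points do not answer is the explicit rule for readmission and placement. Its windows open at discharge, so data collected on in-service events do not enter those outcomes.

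**Conclusion.** The point holds for two service-level outcomes, readmission in RH users and residential placement in RAH users. As defined, they exclude events during reablement, and their comparison between types can mislead if service length or in-service event rates differ. In the illustration the artefact is 5.9 percentage points. That rests on an assumed falling hazard and assumed lengths of 2 and 6 weeks; under a constant hazard, length alone would produce no gap.

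Two stronger conclusions are tempting and unsupported. The first is that the primary EQ-5D-5L comparison is biased by programme length: nothing in the article gives a basis for sizing such a bias. Nor can the QALY illustration be set against the 0.06 in the Sample size section, which is Cohen's f², a ratio of variances and not an EQ-5D difference. The second is that QALYs will in fact cover different lengths of time by type. T0 to T2 does vary with service length, but the article does not say that raw totals over that interval will be compared.

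**What to change.** - Also define readmission (RH) and residential placement (RAH) over a fixed six months from service start (T0), in-service events included, and compare types on that count. Report the post-discharge proportions beside it.
- Take the events from the T1 and T2 questionnaires and the routine service data, with dates. Dates are needed because six-month recall at T1 can reach back to the hospital stay that preceded reablement, which must not be counted as a readmission. For placements, the recall period still to be settled in the pilot should cover the time in the service, or routine data should fill the gap.
- State one common horizon from T0 for any within-study QALY and cost comparison.

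T2 falls at least six months after T0, so the fixed window lies inside the follow-up already planned. The cost is recording event dates and running one extra analysis; no visits or participants are added.
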